**Table 3: SCHEDULE OF ASSESSMENTS: Screening to Day 14.**

### 7.1. Efficacy assessment

- Parasitaemia (thick and thin blood smears) on screening, Days 0 (H0, H8, H16), 1 (H24, H32, H40), 2 (H48, H56, H64), 3 (H72), 4, 5, 6, 7 and 14
- qPCR on screening, Days 0 (H0, H8, H16), 1 (H24, H32, H40), 2 (H48, H56, H64), 3 (H72), 4, 5, 6, 7 and 14

### 7.2. Safety Assessment

- Physical examinations at screening and on H0, H24, H48, H72, and days 4, 5, 6, 7 and 14
- Vital signs, including pulse rate and blood pressure and temperature on screening, Days 0 (H0, H8, H16), 1 (H24, H32, H40), 2 (H48, H56, H64), 3 (H72), 4, 5, 6, 7 and 14
- Haematology, biochemistry analysis at screening, day 3 (H72), day 5, 7 and 14
- PK on Days 0 (H0, H8, H16), 1 (H24, H32, H40), 2 (H48, H56, H64), 3 (H72), 4, 5, 6, 7 and 14
- Recording of adverse events and concomitant medication on all time points

Participants must be seen at all visits on the designated day, or as close to it as possible. Missed or rescheduled visits should not lead to automatic discontinuation.

### 7.3. Exploratory Assessments

- Stool sample at screening and on days 3 (H72) and 7
- Blood sample for membrane feeding at screening, hour 52 representing Cmax of ivermectin (4 hours after last ivermectin treatment), hour 72 and on days 7 and 14

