| Treatment duration      | 
 
- One day ivermectin
 
- Two days ivermectin
 
- Three days ivermectin
 
- Three days placebo
 
                                                                                                                                                                                                                                                                                                                                                                                                                                                                                                                                                                                                                                                                                                                                                                                          |
| Follow-up duration      | 14 days (D1, D2, D3, D4, D5, D6, D7, D14)                                                                                                                                                                                                                                                                                                                                                                                                                                                                                                                                                                                                                                                                                                                                                                                                                                                                                                                     |

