#### **3.3. Safety profile of ivermectin**

Ivermectin has been licensed for human use for almost 30 years, and its safety has been assessed in over 70 trials. More than 2.7 billion 150-200 mcg/kg single doses have been distributed through the Mectizan Donation program (7). In individuals with a high *Loa loa* microfilarial load, Ivermectin can cause severe encephalopathy (6). Outside *Loa loa* endemic areas, the drug is remarkably safe. In onchocerciasis-infected patients, adverse events (AE) to ivermectin are

usually mild, transient, associated with intensity of microfilarial infection and primarily characterized as mild Mazzoti-type reactions to dying microfilaria (8). These effects wane in subsequent administrations (9). No significant dose-response has been found between ivermectin plasma levels and AEs in human dose-ranging studies (10). A recent Cochrane review of ivermectin for river blindness shows that side effects are rarely reported (11). The French authorities recommend up to 400 µg/kg for the control of lymphatic filariasis (12). Some studies showed that also higher doses of ivermectin were well tolerated in adults with multiple doses up to 3 days of 600 µg/kg per day or up to a single dose of 2000 µg/kg (13–16). Currently there is evidence for a three-day course of 300 µg/kg ivermectin to be the most promising regimen for future mass drug administrations (14).

For severe crusted scabies, up to seven 200 µg/kg doses within a month in combination with topical treatment and keratolytics are recommended in the US (17) and Australia (18). The possibility of using more than 3 doses for the treatment of moderate to severe crusted scabies cases is included in the Australian product information (IPC-MK0933-T-062010) (4). Pharmacokinetic investigations of ivermectin single dose (12 mg) showed a Tmax at 4.4 hours post-dose and a half-life of 38.9 hours (31).

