## 4. Trial design

### 4.1. Trial overview

The study is designed as a dose escalation trial with who stapes to assess the safety and efficacy of ivermectin on the reduction of *P. falciparum* parasitaemia in asymptomatic participants in

an endemic area of Gabon. The first stage is an open label trial and included arms I-III. The next stage is a randomized double-blind controlled trial. Potential adult participants living in Lambaréné and in the Tsamba-Magotsi Department, Gabon will be screened for parasitaemia of 200 to 5000 *P. falciparum* parasites/ $\mu$ l without clinical signs of malaria for inclusion in the clinical trial. Participants will be included sequentially in arms I-IV with a pause between arms to allow safety review by DSMB. Each dose escalation stage will only commence after safety assessment of the previous stage and approval by the Data and Safety Monitoring Board. The sponsor can, in consultation with the DSMB, suspend recruitment at any time based on safety considerations.

Study arms:

- Arm I: 5 participants (200  $\mu$ g/kg single dose)
- Arm II: 5 participants (2x200  $\mu$ g/kg)
- Arm III: 5 participants (3x200  $\mu$ g/kg)
- Arm IV:
  - a) 17 participants (3x300  $\mu$ g/kg)
  - b) 17 participants (placebo-control)

All participants will be hospitalized for three days. Assessment during treatment period and follow-up visit will be the same in all study arms.

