#### 6.2.3. Blinding and treatment procedure

One none-blinded person will prepare the treatment assigned by the randomization system, verify that the Participant's treatment group is assigned by the envelope and complete the corresponding treatment record form. Only the person administering ivermectin and placebo would know the groups allocation. Ivermectin and placebo are similar but not identical and will be administered to each participant separately out of the original packaging without changing the labels. All other study personnel (e.g. physicians, microscopists) and study participants will be unaware of the group allocation.

The study drugs will be administered under supervision with a fat containing food such as a croissant with bread spread. These two persons (the person administering the drug and the supervising person) are not otherwise involved in the conduct of the trial. The first dose will be administered at the time of the participant's recruitment into the study. Time between the blood film preparation and treatment administration will be no longer than four hours. Subsequent doses will be given at twenty-four hourly intervals, food will be provided together with the investigational drug.

In the event of vomiting/spitting within one hour of ingestion, the same dose of drug will be re-administered from a supplemental drug supply. However, re-dosing will be done only once per day of treatment administration.

All study treatment taken must be recorded in the CRF, along with any comments about whether the Participants swallowed all or part of the medication.

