## **7. Routine assessment**

All clinical visits and procedures will be undertaken by one investigator of the clinical team. The procedures to be included in each visit are documented in Table 1. Each procedure is assigned a time point and a window period of  $\pm 4$  hours within which the review will be conducted. Participants have to be seen at all visits on the designated day, or as close to it as possible.

| Treatment day                                                                                      |           | 0 |   |    | 1  |    |    | 2  |    |    | 3  | 4  | 5   | 6 | 7 | 14 |
|----------------------------------------------------------------------------------------------------|-----------|---|---|----|----|----|----|----|----|----|----|----|-----|---|---|----|
| Time (hours) after first dose                                                                      | Screening | 0 | 8 | 16 | 24 | 32 | 40 | 48 | 56 | 64 | 72 | 96 | 120 |   |   |    |
| Informed consent                                                                                   | X         |   |   |    |    |    |    |    |    |    |    |    |     |   |   |    |
| Inclusion/ exclusion criteria                                                                      | X         |   |   |    |    |    |    |    |    |    |    |    |     |   |   |    |
| Demography, medical history                                                                        | X         |   |   |    |    |    |    |    |    |    |    |    |     |   |   |    |
| Haematology and biochemistry                                                                       | X         |   |   |    |    |    |    |    |    |    | X  |    | X   |   | X | X  |
| Asexual & gametocyte parasite count (thick & thin blood films)                                     | X         | X | X | X  | X  | X  | X  | X  | X  | X  | X  | X  | X   | X | X | X  |
| Blood in RNA later (for qPCR)                                                                      | X         | X | X | X  | X  | X  | X  | X  | X  | X  | X  | X  | X   | X | X | X  |
| Blood for membrane feeding

*4 hours after last ivermectin treatment together with PK sample | X         |   |   |    |    |    |    |    | X* |    | X  |    |     |   | X | X  |
| Stool sample                                                                                       | X         |   |   |    |    |    |    |    |    |    | X  |    |     |   | X |    |

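### Hour 52 is a 4-hours-post-dose (peak) membrane-feeding sample only in the three-dose arms, and no arm has a listed PK time to match it

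*Protocol*

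**What the plan says.** Section 7.3 lists the membrane-feeding samples as screening, then hour 52 as the ivermectin peak, and continues, from the bracketed explanation of that hour onwards, "4 hours after last ivermectin treatment), hour 72 and on days 7 and 14". One sentence therefore gives a clock time, a pharmacokinetic meaning and a rule relative to dosing. It names no arm.

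Section 4.1 states: "Assessment during treatment period and follow-up visit will be the same in all study arms". Section 6.2.3 sets the dose interval: "Subsequent doses will be given at twenty-four hourly intervals". The Synopsis gives treatment durations from "One day ivermectin" up to three days, so Arm I has one dose, Arm II two, and Arms III, IVa and IVb three (placebo in IVb).

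Table 3 in section 7 has no hour-52 column. The starred mark stands under H56, and its footnote reads "4 hours after last ivermectin treatment together with PK sample". Section 7 gives every procedure a window of plus or minus 4 hours.

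Section 7.2 lists "PK on Days 0 (H0, H8, H16), 1 (H24, H32, H40), 2 (H48, H56, H64), 3 (H72", followed by days 4 to 7 and 14. The PK row of Table 3 has the same times. Section 3.3 reports Tmax "at 4.4 hours post-dose and a half-life of 38.9 hours" after a single 12 mg dose.

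**The concern.** The clock time and the dosing rule in 7.3 agree only when the last dose is given at hour 48. In the one- and two-dose arms, staff cannot follow both. If they follow the clock, the sample is no longer what 7.3 calls it.

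A second gap affects every ivermectin arm. A feed labelled as a peak sample is useful mainly if the concentration at that moment is measured. The footnote intends this, but the PK times that staff would work from do not include it.

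At stake is the reading of the exploratory mosquitocidal objective in 4.2.3. A weaker effect at hour 52 in Arm I or II could come from fewer doses, from a longer interval since the last dose, or from both. Even the three-dose feeds could end up without a concentration taken at the same time.

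**Working it through.** **Inputs.** Dose interval 24 h (6.2.3). Doses per arm: 1, 2, 3, 3 and 3 for I, II, III, IVa and IVb (Synopsis, 4.1). Sample at hour 52, 4 h after the last dose (7.3). Window ±4 h (section 7). Tmax 4.4 h and half-life 38.9 h (3.3).

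**Step 1: reproduce hour 52.** Hour of last dose = 24 × (number of doses − 1). Sample hour = last dose + 4.

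- Three doses: 24 × 2 + 4 = 52, the stated hour.
- Two doses: 24 × 1 + 4 = 28.
- One dose: 24 × 0 + 4 = 4.

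**Step 2: hours since the last dose if every arm is sampled at the same clock time.**

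| Arm | Last dose | At H52 | At H56 | At H72 |
|---|---|---|---|---|
| I | H0 | 52 | 56 | 72 |
| II | H24 | 28 | 32 | 48 |
| III, IVa, IVb | H48 | 4 | 8 | 24 |

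**Step 3: size in terms of exposure.** Assume mono-exponential decline from the last peak. Share of the arm's own peak = 2^(−(t − 4.4)/38.9), with t the hours since the last dose.

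- Arm I at H52: 2^(−47.6/38.9) = 0.43.
- Arm II at H52: 2^(−23.6/38.9) = 0.66.
- Three-dose ivermectin arms at H52: t = 4 is just before Tmax, so about 1.
- Three-dose ivermectin arms at H56: 2^(−3.6/38.9) = 0.94.

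A one-compartment oral model with superposition, using the same Tmax and half-life, gives 44%, 66% and about 100% at H52, and 94% for the three-dose arms at H56. Both calculations assume that single-dose, linear kinetics carry over to these regimens.

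**Step 4: Table 3.** The cells in the membrane-feeding row run screening, H0, H8, H16, H24, H32, H40, H48, H56. The starred mark is the ninth cell, H56. The other marks in the row fall at screening, H72, day 7 and day 14, as 7.3 says, so the column alignment can be trusted. With ±4 h, an H56 slot spans H52 to H60, which is 4 to 12 h after the third dose. An H52 slot would span H48 to H56, from the third dose itself to 8 h after it.

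**Step 5: PK times.** The first listed time after each dose is H8 − H0 = 8 h, H32 − H24 = 8 h and H56 − H48 = 8 h. H4, H28 and H52 are all absent, although the quoted Tmax is 4.4 h.

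**Step 6: who is affected.** The timing problem touches Arms I and II: 5 + 5 = 10 participants, out of 15 in the escalation stage and 49 in the trial. The missing PK time applies to all arms.

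**The case against.** Section 7.3 does not itself say that hour 52 applies to all arms; that follows from the general sentence in 4.1. The hour-52 sample entered with Version 4 of 24 June 2019, while the planned period began in April 2019 and the arms run in sequence. The protocol does not show whether Arms I and II were still open. This makes the practical reach uncertain, but nothing in the current text limits hour 52 to the later arms.

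A reader might infer that Table 3 and 7.3 conflict outright. They do not: the footnote repeats the 4-hour rule, and H52 is the edge of the H56 window. It is a mismatch of nominal times. The footnote also asks for a PK sample, so the intention is present. What is missing is that time in the PK row and in 7.2.

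A reader might also infer that sampling time is confounded with dose throughout the trial. The documents do not support that. Arms III, IVa and IVb all have hour 52 at 4 h after the last dose, so the randomised comparison and 3x200 versus 3x300 µg/kg have equal timing. What varies with time since last dose is the number of doses, in Arms I and II.

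Finally, the mosquitocidal objective is exploratory, no between-arm feeding comparison is named, Arms I–III are descriptive and not randomised, and the stated PK objective concerns efficacy and safety. A concentration–effect analysis can use any feed with a measured concentration, and the H72, day 7 and day 14 feeds coincide with listed PK times. All of this stands and limits the impact. It does not make the peak label correct in Arms I and II, nor supply a listed concentration for the hour-52 feed.

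**Conclusion.** The point holds within limits. Read with 4.1, the description of hour 52 as a peak sample 4 h after the last dose is right for the three-dose arms and wrong by 48 h in Arm I and 24 h in Arm II. The size, about 43% and 66% of each arm's own peak, rests on the quoted 12 mg single-dose kinetics and mono-exponential decline. It measures how late the sample is, not bias in a planned result.

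Separately, no arm has a listed PK time between a dose and 8 h after it. The paired concentration that the footnote calls for is therefore absent from the operative PK schedule, including in the randomised stage.

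The consequence is confined to the exploratory mosquitocidal assessment and its link to concentration. The efficacy endpoints in section 8 are parasitaemia measures and do not depend on this sample. The correction is worth making because it changes what is drawn, when it is drawn and what it may be called.

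**What to change.** Reconcile 7.3, Table 3 and 7.2:

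- State whether the anchor is hour 52 or 4 h after each arm's own last dose. The second means H4 in Arm I, H28 in Arm II and H52 in the three-dose arms. For the placebo arm, refer to the last study dose.
- Show the sample at that time in Table 3, with a window narrow enough to keep it near that time. The general ±4 h is as long as the interval from dose to sample.
- List the paired PK sample at the same time in the PK row and in 7.2.
- If Arms I and II were sampled at hour 52, do not label or analyse those feeds as peak samples. Report them by actual time since last dose.

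The cost is an amendment to the schedule and the PK list. All three possible times fall within the hospital stay of at least 72 hours (section 9), so no visit is added, and the footnote already intends the paired sample. Confirm that the approximate blood volume in 10.1 covers it.

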## 8. Endpoints

### 8.1. Primary Efficacy Endpoint

1. Time to 90% parasite reduction for at least 8 hours assessed by microscopy

### 8.2. Secondary Efficacy Endpoints

1. Time to 90% parasite reduction assessed by qPCR

2. Difference in AUC of parasitaemia until D7
3. Parasite clearance time, defined as time to parasitaemia <100 parasites/mL

### **8.3. Primary Safety Endpoint**

1. Number and occurrence of related SAE and Grade 3 AE from time of first administration of ivermectin until the end of the study

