### 4.2.2. Secondary objectives

- To compare efficacy of ivermectin 200 $\mu$ g/kg single dose versus two-day 200 $\mu$ g/kg treatment versus three-day 200 $\mu$ g/kg treatment versus three-day 300 $\mu$ g/kg treatment
- To compare efficacy of ivermectin three-day 300 $\mu$ g/kg treatment compared to placebo
- To compare safety and tolerability of ivermectin 200 $\mu$ g/kg single dose versus two-day 200 $\mu$ g/kg treatment versus three-day 200 $\mu$ g/kg treatment versus three-day 300 $\mu$ g/kg treatment
- To compare safety and tolerability of ivermectin three-day 300 $\mu$ g/kg treatment compared to placebo

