### 6.2. Treatment

#### 6.2.1. Treatment arms

Participants fulfilling all inclusion criteria and none of the exclusion criteria will be assigned sequentially to receive ivermectin 200 µg/kg orally single dose for one (5 first subjects), two or three days (10 next available subjects). Following interim safety analysis, 34 subjects will be randomly allocated in two treatment arms to receive either 300 µg/kg per day for 3 days or placebo for 3 days. There will be four consecutive study arms (arms IV a) and b) will be parallel):

- Arm I: 5 participants (200 µg/kg single dose)
- Arm II: 5 participants (2x200 µg/kg)

- Arm III: 5 participants (3x200 µg/kg)
- Arm IV:
  - a) 17 participants (3x300 µg/kg)
  - b) 17 participants (placebo-control)

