### **8.4. Secondary Safety Endpoint**

1. Number and occurrence of any AE from time of first administration of ivermectin until the end of the study

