## **10. Potential risks for participants**

### **10.1. Phlebotomy**

The maximum volume of blood drawn over the study period is approximately 300 ml over 14 days. Additional blood samples could be required for safety reasons. However, this volume should not compromise these participants. There may be minor bruising, local tenderness or presyncopal symptoms associated with venepuncture, which will not be documented as AEs if they occur. Rare possible side effects are infections, thrombophlebitis and neural lesions.

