### 12.1. Definitions

**Adverse Event (AE):** An AE can therefore be any unfavourable and unintended sign (including an abnormal laboratory finding), symptom or disease temporally associated with the study, whether or not considered related to the study interventions.

**Adverse Reaction (AR):** An AR is any untoward or unintended response to ivermectin. This means that a causal relationship between ivermectin and/or *Plasmodium* infection and an AE is at least a reasonable possibility, i.e., the relationship cannot be ruled out. All cases judged by either the reporting medical investigator or the sponsors as having a reasonable suspected causal relationship to ivermectin and/or *Plasmodium* infection will be qualified as adverse reactions.

**Unexpected Adverse Reaction:** An unexpected adverse reaction is where the nature or severity of the adverse reaction is inconsistent with that expected for the intervention.

**Serious Adverse Event (SAE):** To ensure no confusion or misunderstanding of the difference between the terms "serious" and "severe", which are not synonymous, the following note of clarification is provided: The term "severe" is often used to describe the intensity (severity) of a specific event (as in mild, moderate, or severe myocardial infarction); the event itself, however, may be of relatively minor medical significance (such as severe headache). This is not the same as "serious," which is based on Participant/event outcome or action criteria usually associated with effects that pose a threat to a participant's life or functioning. Seriousness (not severity) serves as a guide for defining regulatory reporting obligations.

An SAE is an adverse event that results in any of the following outcomes:

- death;
- a life-threatening adverse event;
- inpatient hospitalization or prolongation of existing hospitalization;

- a persistent or significant disability/incapacity;
- a congenital anomaly/birth defect.

`Life threatening` refers to an adverse effect that at occurrence represented an immediate risk of death to the participant; it does not refer to an event that hypothetically might have caused death if it were more severe. Similarly, a hospital admission for an elective procedure is not considered a Serious Adverse Event.

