### **12.3. Reporting procedures for AEs (Excluding SAEs)**

All AEs occurring during the study, since the signature of the Informed Consent Form until the end of the follow up period, observed by the investigator or reported by the participant will be recorded in the CRF. Malaria events occurring at any time during the study will be recorded as an AE.

AEs that result in a participant's withdrawal from the study or that are present at the end of the study will be followed up (if participant's consent to this) until a satisfactory resolution or stabilization occurs, or until a non-study related causality is assigned.

**Grade 1** Mild: Transient or mild discomfort (< 48 hours); no medical intervention/therapy required;

**Grade 2** Moderate: Mild to moderate limitation in activity - some assistance may be needed; no or minimal medical intervention/therapy required;

**Grade 3** Severe: Marked limitation in activity, some assistance usually required; medical intervention/therapy required, hospitalization possible;

**Grade 4** Potentially life threatening: Extreme limitation in activity, significant assistance required; significant medical intervention/therapy required, hospitalization or hospice care probable.

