### **12.6. Safety hold of the study and stopping rules**

The study may be placed on safety hold for the following reasons

- On advice of the safety monitor;
- On advice of the investigators;
- On advice of the EC
- One or more participants experience a SAE that is determined to be related to the study product administration;
- One or more grade 3 or higher adverse events which are unexpected and possibly or probably related to the drug administration.

If the study is placed on hold it may only be restarted following discussion with and approval from the Safety monitor, the sponsor and study investigators.

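### The primary safety endpoint leaves out non-serious Grade 4 events, and both safety endpoints start at an ivermectin dose that placebo participants never receive

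*Protocol*

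**What the plan says.** The primary safety endpoint (section 8.3, repeated in the synopsis) is "Number and occurrence of related SAE and Grade 3 AE from time of first administration of ivermectin until the end of the study". The secondary one (section 8.4, also in the synopsis) is "Number and occurrence of any AE from time of first administration of ivermectin until the end of the study". Section 4.2.2 makes the safety comparison of the three-day 300 µg/kg course with placebo a secondary objective, and Arm IVb consists of 17 participants on placebo only (section 6.2.1).

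The surrounding rules are:

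- **Grading (12.3).** There are four grades. The highest is "Potentially life threatening: Extreme limitation in activity, significant assistance required".
- **Hold rule (12.6).** One possible reason for a hold is "One or more grade 3 or higher adverse events", if unexpected and possibly or probably related to the drug.
- **Recording (6.1, 12.3).** AEs are recorded from consent to the end of follow-up. Section 4.1 gives all arms the same assessments.
- **Relatedness.** Section 12.1 says that events suspected to be caused by ivermectin and/or *Plasmodium* "infection will be qualified as adverse reactions". Section 12.2 defines an intervention-related AE by its relationship to the study intervention alone.
- **Phlebotomy (10.1).** The text mentions "presyncopal symptoms associated with venepuncture, which will not be documented as AEs if they occur".

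**The concern.** Safety and tolerability is the first primary objective, and a DSMB safety review stands before each dose step. An endpoint that names one severity grade when the scale has a higher one can leave out the more severe event. An endpoint whose clock starts at a drug that the control arm does not get gives that arm no rule for what to count. If neither is settled beforehand, the severity threshold and the placebo start time have to be chosen later by the analyst, possibly with the data in view, and any sensible choice departs from the protocol's own wording.

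**Working it through.** **Plan's own figures.** The protocol gives no figure for the safety comparison with placebo. The two figures it does give can be checked, and neither depends on the endpoint wording.

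- Synopsis, arms of five, AE of 50% prevalence: 1 − 0.5^5 = 0.969, against the stated 95%.
- Section 5.1, 17 events: hazard ratio = ln(0.25)/ln(0.75) = 4.82; events = 4 × (1.960 + 1.282)² / (ln 4.82)² = 17.0. With 17 per arm, expected events = 17 × 0.25 + 17 × 0.75 = 17.

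**Grade 4.** The table shows where a non-serious Grade 4 AE goes when it is unexpected and possibly or probably drug-related.

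| Rule | Counted? |
|---|---|
| 12.6 hold criterion | Yes |
| 8.4 secondary endpoint (any AE) | Yes |
| 8.3, SAE part | No, it is not serious |
| 8.3, Grade 3 part | No, it is Grade 4 |

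Such an event is possible under the protocol's definitions. For an SAE, section 12.1 takes life-threatening to mean immediate danger of death when the event occurs and rules out hypothetical danger; Grade 4 needs only potential danger. Hospital admission is an SAE criterion, but every participant is already an inpatient for at least 72 hours (section 9). An event managed within that stay, without prolonging it, does not meet that criterion.

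Section 8.3 also does not settle whether *related* qualifies Grade 3 AEs as well as SAEs. If it qualifies SAEs only, an unrelated Grade 4 AE is lost while an unrelated Grade 3 AE is counted.

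**Window.** Arms I to III and IVa: the start is the first ivermectin dose, which is defined. Arm IVb: no ivermectin is given, so there is no start. This affects 17 of 49 participants, or 17 of the 34 randomised. The consent-based recording window in 12.3 does not fill the gap, because consent precedes the first dose.

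As an outer bound, suppose that the literal wording were applied, no placebo AE were counted and both arms had the same true AE rate. The rates are assumptions; the documents give none for this trial. In a two-sided Fisher test at 5% with 17 v 17, 4 v 0 gives p = 0.103 and 5 v 0 gives p = 0.044, so five ivermectin cases suffice for a false difference.

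| Assumed AE rate in both arms | False difference, literal window | Common first-dose window |
|---|---|---|
| 10% | 2% | 0.8% |
| 20% | 24% | 1.9% |
| 30% | 61% | 2.0% |
| 40% | 87% | 2.2% |
| 50% | 98% | 2.4% |

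**Presyncope.** Section 10.3 lists dizziness (2.8%) and orthostatic hypotension (1.1%) as ivermectin reactions in other patient groups. Taking these as assumed rates, P(at least one case in 17) = 1 − (1 − p)^17: 17% at p = 1.1%, 38% at 2.8% and 49% at their sum of 3.9%. The expected number is at most 17 × 0.039 = 0.7, so few events are at stake.

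**The case against.** The strongest reply is that the window is a drafting slip. Section 9 calls day 0 the day of ivermectin administration for everyone, and the schedule of assessments counts hours from the first dose in all arms. Staff other than those preparing and giving the drug are blinded and could not apply different windows. Ivermectin then plainly stands for study drug. This largely stands: nothing suggests that an analyst would count zero placebo AEs, so the false-difference rates show only what the literal text would do. It does not justify leaving an endpoint definition that has no meaning in one arm of a planned comparison.

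On Grade 4, the reply is that the grade itself makes hospital care probable, and section 12.1 lets medical judgement class other important events as serious, so most related Grade 4 events would enter as SAEs. That also stands, and it makes the gap narrow. It does not close it.

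Four stronger readings are tempting, and the documents do not support them:

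- *Placebo safety data are missing or the comparison is invalid.* AEs are recorded in every arm from consent, on a common schedule.
- *Malaria symptoms count as drug reactions and mask toxicity.* The endpoint uses the word related, which section 12.2 ties to the intervention. Malaria enters only if related is read through the looser definition in 12.1.
- *Laboratory toxicity can never reach Grade 3.* A laboratory event that needs medical intervention can.
- *Almost any presyncope will go unrecorded.* Section 10.1 covers only symptoms associated with venepuncture, in both arms alike.

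**Conclusion.** The point holds as two faults in endpoint wording. Section 8.3 and the synopsis omit a Grade 4 AE that meets no SAE criterion; the omission is confined to the primary endpoint, and how many events it affects cannot be estimated from the protocol. Sections 8.3, 8.4 and the synopsis leave the counting window undefined for the 17 placebo participants, without any loss of data.

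Three lesser matters remain. The definitions in 12.1 and 12.2 conflict on whether infection-caused events are reactions. Section 10.1 conflicts with the rule in 12.3 that all AEs are recorded. The grades in 12.3 have no numeric criteria for laboratory AEs, so a symptom-free abnormality that needs no intervention does not fit Grade 3, although abnormal laboratory findings are AEs under 12.1.

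The conclusion rests on the protocol text alone; the rates used above are illustrative assumptions. The 17 events, 17 per randomised arm and 5 per escalation arm are unaffected.

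**What to change.** - In 8.3, 8.4 and the synopsis, start the window at the first dose of study drug (ivermectin or placebo).
- In 8.3 and the synopsis, replace Grade 3 with Grade 3 or higher.

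In the same amendment:

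- State that related in 8.3 means intervention-related as in 12.2, say whether it qualifies both SAEs and graded AEs, and reconcile 12.1 with it.
- Reconcile 10.1 with 12.3 on presyncope associated with venepuncture.
- State how laboratory AEs are graded, or point to the document that says so.

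The two main changes cost a few words, need no new data and leave the sample size as it is. The presyncope point may add a few minor AE records, depending on how it is resolved.
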